#### Exclusion criteria

Travelling (including overseas/interstate) for more than 3 weeks within the next 12 weeks.Unable to attend the scheduled week 6 and week 12 visits.Report contraindications to mouthwash or food dyes such as allergy.Report long-term use (i.e. 4 weeks or more) of antibiotics.Not willing to stop using their current mouthwash for the next 12 weeks.Previously enrolled into the OMEGA study.Men who know someone in their household who is currently enrolled in the OMEGA study. This is to prevent mixing the allocated mouthwashes between participants.Individuals who are transgender.

### Trial settings and locations

Participants will be recruited from four large urban publicly-funded sexual health centres in Melbourne and Sydney in Australia: Melbourne Sexual Health Centre, Sydney Sexual Health Centre, Western Sydney Sexual Health Centre, RPA Sexual Health; and one GP clinic that see a high proportion of MSM in Melbourne: Northside Clinic. Potentially eligible participants will be identified by the clinicians and referred to the research nurse who will explain the study and check eligibility using the paper-based eligibility screening template. Eligible participants will be given a participant information sheet and will be asked to provide written information consent prior to commencing the study.

### Intervention

Participants will be randomly allocated to one of two mouthwash solutions. Both are alcohol free commercial mouthwash products that are widely available in supermarkets and pharmacies in Australia – one is commercially advertised to be antibacterial (mouthwash A) and the other is not (mouthwash B). In our in-vitro study, we found that mouthwash A demonstrated an inhibitory effect against *N. gonorrhoeae* on culturing oropharyngeal swabs; this was not the case for mouthwash B.

Participants will receive a total of four study mouthwash bottles (2 × 500 mL bottles at baseline and 2 × 500 mL bottles at week 6) and will be asked to rinse and gargle 20 mL for 60 seconds at least once a day. Rinsing and gargling is important because our previous work has shown that gonorrhoea is detected at both the tonsillar fossae and the posterior oropharynx in MSM [89]. Figure 1 illustrates how to rinse and gargle a mouthwash, and this instruction sheet will be provided to all participants. A video clip is also available on the OMEGA study website for participants to review the procedure (www.mshc.org.au/omega). Participants can use the study mouthwash more than once a day but not more than five times a day. All participants will be required to stop using any other mouthwash they are currently using, during the study period.

**Fig. 1 Fig1:**
[figure not shown]
An instruction sheet illustrating the procedure of using the study mouthwash

#### Extra bottles

All participants will be allowed to request extra bottles at any time between week 0 and week 12. The number of extra bottles given to the participants and reasons will be recorded by the research nurse at each site.

### Outcomes

#### Primary outcome

The primary outcome of this trial is the proportion of MSM diagnosed with oropharyngeal gonorrhoea and the cumulative incidence of oropharyngeal gonorrhoea diagnosed by NAAT at any time point within 12 weeks. We will use NAAT to determine the primary outcome rather than culture because NAAT has a higher sensitivity than culture at the oropharynx [89–91].

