**Methods/design:**

The OMEGA (Oral Mouthwash use to Eradicate GonorrhoeA) study is a double-blind RCT and will be conducted at several sexual health clinics and high caseload General Practice (GP) clinics in Melbourne and Sydney, Australia. A total of 504 MSM attending the participating sites will be recruited. Participants will be randomised to either using ‘Study mouthwash A’ or ‘Study mouthwash B’ for 12 weeks. Study mouthwash A was inhibitory against *N. gonorrhoeae* in vitro, whereas study mouthwash B was not. Participants will be instructed to rinse and gargle the study mouthwash for 60 seconds every day. The primary outcome is the proportion of participants with oropharyngeal gonorrhoea detected by nucleic acid amplification test by 12 weeks.

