
We hypothesise that it is important to reduce the prevalence and incidence of oropharyngeal gonorrhoea to reduce the overall burden of gonorrhoea [48]. This is because both the prevalence and incidence of gonorrhoea is largely driven by infections at anatomical sites where infections are predominantly asymptomatic, and therefore undetected and untreated, allowing ongoing transmission. In MSM, gonococcal infections at extra-genital sites (i.e. oropharynx and anorectum) are mainly asymptomatic [73–76]. This is also supported by recent mathematical modelling suggesting approximately 75% of incident cases of oropharyngeal gonorrhoea were transmitted from oropharynx to oropharynx through kissing [77], adding weight to another model which suggests gonorrhoea may not be eliminated from the MSM population even with 100% condom-use for anal sex [78]. The implications of these findings for the control of gonorrhoea are clear. If major reductions in gonorrhoea are to be achieved in MSM population, it is essential to reduce gonorrhoea transmission from the oropharynx.

Options for reducing oropharyngeal gonorrhoea cases include use of condoms for oral sex, very frequent screening, antibiotic prophylaxis or use of other agents that could act to prevent the acquisition of infection such as our proposed mouthwash intervention. Given that condom use for anal sex is decreasing [79–81] and MSM rarely use them for oral sex [82], the 3-month average duration of gonorrhoea means that screening would need to be at least every 3 months, as recommended for high-risk Australian MSM [83] but this has been shown to be difficult for MSM to sustain [84]. Antibiotic prophylaxis is unlikely to be adopted because of concerns about emerging resistance. There is no vaccine against gonorrhoea [85]. Thus, mouthwash represents a novel and attractive alternative intervention.

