#### Saliva

Participants will be required to self-collect a saliva sample every 3 weeks. Figure 4 illustrates how to self-collect a saliva sample. This instruction sheet will be given to the participants and a video clip is available on the OMEGA study website for participants to review the procedure (www.mshc.org.au/omega). In brief, participants will be instructed to accumulate saliva in the mouth for about 30 seconds to get a reasonable volume of saliva. Participants will spit as much saliva as possible into a yellow cap specimen collection jar, and saliva will be collected by using an UriSwab (Copan Diagnostics, Brescia, Italy). Saliva samples at week 6 and week 12 will be collected at the participating clinic under the research nurse’s supervision; while saliva samples at week 3 and week 9 will be collected at home by participants. All saliva specimens collected will be transported by using UriSwab.

All participants will be required to send their home-based collected UriSwabs to the Melbourne Sexual Health Centre at week 3 and 9 by post. The research nurse at each participating clinic will be required to send clinic-based collected UriSwabs to the Melbourne Sexual Health Centre at week 6 and 12 by post.

Once the research team at the Melbourne Sexual Health Centre receives the UriSwab by post, the UriSwab will be immediately centrifuged at 1200 g for 1 min to separate the saliva from the UriSwab sponge. The centrifuged saliva will be pipetted into a sterile 2.0 mL micro tube (Scientific Specialties, Inc., CA, USA) and stored at −80 °C freezer at the Melbourne Sexual Health Centre for testing.

All centrifuged saliva samples will be batch tested at the Royal Women’s Hospital, Molecular Microbiology Laboratory, Melbourne. The saliva samples will be placed on the MagNA Pure 96 Instrument (Roche Diagnostics, Mannheim, Germany) for DNA purification and will be assessed for sampling and extraction adequacy by amplifying a 260 bp region of the human beta-globin gene [95]. The gonococcal bacterial DNA load of the sample will be quantified using qPCR assays targeting the *N. gonorrhoeae opa* gene. All samples positive for the *opa* gene will then be confirmed using a qPCR targeting the *N. gonorrhoeae porA* gene [96, 97].

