#### Primary analysis

The primary end-point will be the proportion of men who have gonorrhoea detected in the oropharynx by NAAT at any time within 12 weeks in any specimen (saliva and/or oropharyngeal swabs). The proportion of men with oropharyngeal gonorrhoea detected will be compared between both groups. The 95% confidence intervals (CI) of the proportion of men with oropharyngeal gonorrhoea will be calculated based on the ‘exact’ binomial confidence intervals [106]. The two study arms will be compared using logistic regression. Multivariate logistic regression will be performed to adjust any imbalance of baseline characteristics and potential confounding factors. Men with symptomatic urethral gonorrhoea may attend clinical services between the two clinic visits and test positive for oropharyngeal gonorrhoea. Any positive oropharyngeal results will be included in the analysis unless they were taken within 3 weeks of treatment because within 3 weeks NAAT results may represent residual non-viable DNA from the previous infection [107].

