#### Secondary analysis

The cumulative incidence of oropharyngeal gonorrhoea by week 12 will also be calculated. Treatment arms will be compared using survival analysis, clustered by each individual to allow for multiple events. Individuals who tested positive for oropharyngeal gonorrhoea during the study period will be treated and remain in the study until end of week 12. Individuals will contribute at least two time periods of follow-up (i.e. time between each test).

The proportion of men who have gonorrhoea detected in the oropharynx by culture within 12 weeks will also be calculated as a secondary outcome, the statistical approach will be the same used for the primary analysis. A sensitivity analysis will also be performed comparing treatment arms in terms of gonorrhoea detection at 6 or 12 weeks using repeated measures logistic regression methods.

The adherence to mouthwash over 12 weeks will be collected from the questionnaire every 3 weeks. The number of days using mouthwash over the 12-week period will be calculated for each participant, and stratified by treatment arm.

Acceptability and tolerability of using mouthwash over 12 weeks will be measured. Participants will be asked about any discomfort and difficulties in using the mouthwash every 3 weeks.

The proportion of men who have other STIs (i.e. gonorrhoea at other site except at the oropharynx, chlamydia, HIV and syphilis) by 12 weeks will also be calculated as a secondary outcome and stratified by treatment arm.

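### Cumulative incidence is part of the primary outcome in one section and a secondary analysis in another, and its repeat-event analysis could count one untreated infection more than once

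*Protocol article*

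**What the plan says.** **Primary outcome.** In the Protocol article, Outcomes (Primary outcome) gives two quantities: "the proportion of MSM diagnosed with oropharyngeal gonorrhoea and the cumulative incidence of oropharyngeal gonorrhoea diagnosed by NAAT at any time point within 12 weeks". Three other places point to the proportion alone:

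- Abstract, Methods/design: "The primary outcome is the proportion of participants with oropharyngeal gonorrhoea detected by nucleic acid amplification test by 12 weeks".
- Primary analysis, under Statistical methods: "The primary end-point will be the proportion of men who have gonorrhoea detected in the oropharynx by NAAT at any time within 12 weeks". Any saliva or swab specimen counts, and the arms are compared by logistic regression.
- Sample size: a comparison of two proportions, 20% against 10%, giving 438 men.

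Cumulative incidence next appears under Secondary analysis: "The cumulative incidence of oropharyngeal gonorrhoea by week 12 will also be calculated". It is missing from the list under Secondary outcomes.

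**Repeat-event analysis.** Secondary analysis continues: "Treatment arms will be compared using survival analysis, clustered by each individual to allow for multiple events". Follow-up is split into the periods between tests, and "Individuals who tested positive for oropharyngeal gonorrhoea during the study period will be treated and remain in the study".

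**Specimens and results.** In Table 2, saliva is the only specimen at weeks 3 and 9; swabs are taken at weeks 6 and 12. The Saliva section stores samples at −80 °C and says "All centrifuged saliva samples will be batch tested". The Oropharyngeal swabs section promises participants their results for weeks 6 and 12, with recall of positives for treatment. It promises nothing for weeks 3 and 9. The one exclusion of a positive, under Primary analysis, covers specimens taken within 3 weeks of treatment. The Background refers to "the 3-month average duration of gonorrhoea".

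**The concern.** The two quantities joined under Primary outcome are not two names for one thing. The proportion is one yes/no per man. Cumulative incidence, as analysed, allows several events per man in a clustered survival model. The two can give different answers, and the protocol does not say which decides the trial. A choice made after the results are known would weaken the primary claim.

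The second point concerns what the incidence analysis measures. The aim is to reduce acquisition. If a man is positive on saliva at week 3, nobody knows it, and he is still positive at week 6, a test-to-test analysis without a rule for new events could record two events for one infection. The comparison would then mix persistence with acquisition.

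**Working it through.** **1. Which outcome the sample size supports**

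Inputs (Sample size): 20% and 10%, 5% significance (two-sided assumed), 80% power, 1:1 allocation.

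Uncorrected size per arm: n = [1.960·√(2·0.15·0.85) + 0.842·√(0.2·0.8 + 0.1·0.9)]² / 0.10² = (0.990 + 0.421)² / 0.01 ≈ 199.0.

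With continuity correction: (n/4)·[1 + √(1 + 4/(n·0.10))]² = 49.74 × (1 + 1.096)² ≈ 218.5, so 219 per arm and **438 in total**, as stated. The same formula reproduces all six cells of Table 1 (438/572, 356/464, 294/380). The trial is therefore sized on the proportion alone at the full 5%.

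**2. If both quantities were primary and either could claim success**

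Testing each at 5%, the type I error is at most 10% (Bonferroni bound) and 1 − 0.95² = 9.75% if they are independent. For two correlated normal statistics it is 1 − P(|Z₁| < 1.96 and |Z₂| < 1.96):

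| Assumed correlation | Type I error |
|---|---|
| 0.7 | 8.3% |
| 0.8 | 7.8% |
| 0.9 | 7.0% |

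The protocol gives no correlation, so these are illustrations. Splitting alpha to 2.5% each would need 522 evaluable men for the proportion (continuity-corrected), and 219 per arm would have about 71% power.

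**3. Persistence between successive tests**

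Assume exponential duration with mean m weeks and perfect detection. An untreated man positive at week 3 is still positive at week 6 with probability p = exp(−3/m). Because the Background gives both resolution in under 12 weeks and a 3-month average, a range is shown.

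Now assume also that onset is uniform over 12 weeks, that all four tests define events, that saliva results are not acted on, and that a man is treated one week after a positive swab. Infections starting in weeks 0–3 or 6–9 (half of them) meet saliva first and can be positive again at the following swab visit. Those starting in weeks 3–6 or 9–12 meet a swab first and give one positive. Detection at the first test after onset has the same chance in each interval, so among detected infections the share positive twice is p/2, and the mean number of positives is 1 + p/2.

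| Mean duration m (weeks) | p | Positive twice, p/2 | Positives per infection |
|---|---|---|---|
| 6 | 0.61 | 30% | 1.30 |
| 9 | 0.72 | 36% | 1.36 |
| 12 | 0.78 | 39% | 1.39 |
| 13 | 0.79 | 40% | 1.40 |

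At m = 12, the repeats are 0.39/1.39 = 28% of all counted positives.

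**4. Swabs only**

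If only the week 6 and week 12 swabs define events, a man positive at week 6 is treated before week 12 under the same assumptions, and the share counted twice is 0%. Section 3 therefore depends on saliva entering the analysis.

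**5. Does the existing exclusion help?**

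The 3-week window starts at treatment. A man whose saliva positive was not acted on has no treatment date, so the window cannot remove his second positive.

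**The case against.** The protocol speaks of the primary outcome in the singular, and the abstract, sample size and Primary analysis agree on the proportion. A reader might infer from the Outcomes section that success on either quantity would do, and hence that type I error is 7–8%. The protocol does not say that, so the inflation is conditional. The contradiction still stands, because one section defines the primary outcome differently from the rest.

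A reader might also infer that the survival analysis will count one infection as several events. The text does not go that far:

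- It allows multiple events but does not say that a persisting positive is a new one. An analysis plan that is not shown may define this.
- It does not name the specimens for this analysis. Its minimum of two periods per man also fits the two swab visits.
- Under the assumptions above the count is at most two. More would need an infection that saliva detects and swabs miss.
- No batch interval is given, and nothing says that saliva results are withheld. The timing is unstated.

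Finally, the binary endpoint counts each man once, clustering by individual is already planned, and duplication at equal rates in both arms would leave a rate ratio roughly unchanged. Distortion between arms requires the mouthwash to alter duration or detection, and its size is not estimated here. These points limit the concern. They do not remove the tension between an analysis that presumes treatment after a positive test and a saliva procedure that does not ensure it.

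**Conclusion.** The contradiction about the primary outcome is certain, since it is visible in the text, and it should be settled before unblinding. No stated number is wrong because of it: 438 is correct for the proportion as sole primary outcome.

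The repeat-event point is real but conditional, and confined to the secondary analysis. If saliva positives define events and no rule for a new event applies, 61–79% of untreated week 3 positives would be positive again at week 6, and about 30–40% of detected infections would be counted twice. Both ranges assume exponential duration with mean 6–13 weeks; the second also assumes uniform onset, perfect detection and no action on saliva results. The primary comparison of proportions is not affected by this.

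**What to change.** 1. Under Primary outcome, name the proportion with any positive oropharyngeal NAAT by week 12 as the single primary outcome, and add cumulative incidence to Secondary outcomes. This is a wording change and leaves the sample size as it is.
2. Under Secondary analysis, state which specimens define events in the survival analysis.
3. Count a repeat positive as a new event only after an intervening negative specimen, or when it is taken more than 3 weeks after recorded treatment, the window the protocol already uses under Primary analysis. One false negative could still create a spurious event, so report how many new events rest on a single negative.
4. Reconcile the Saliva, Oropharyngeal swabs and Secondary analysis sections on whether saliva positives are known and treated before the next test.

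No new data are needed. The price is fewer counted events in the secondary analysis: up to about 28% under the 12-week illustration, and close to none if only swabs define events.

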#### Secondary outcomes

There are several secondary outcomes in this trial.Proportion of MSM diagnosed with oropharyngeal gonorrhoea by culture within 12 weeks.Adherence to mouthwash over 12 weeks.Acceptability and tolerability of using mouthwash.The proportion of MSM with any of: gonorrhoea at other anatomical sites (urethra and anorectum) or newly acquired chlamydia, HIV or syphilis infection by week 12.

### Sample size

Sample size and power calculations were performed using Stata to compare two proportions (version 13 Stata Corp., College Station, TX, USA) [92, 93]. A previous study has shown that about 10% of MSM had a repeat culture positive for gonorrhoea within 12 weeks after a culture positive for gonorrhoea [88]. With NAAT is a more sensitive test and its detection rate five times higher compared to culture [56], we assumed oropharyngeal gonorrhoea positivity by NAAT in the arm using mouthwash B to be 20% over 12 weeks. Table 1 shows the number of participants required to detect a 50% reduction in oropharyngeal gonorrhoea positivity from 20% in the control arm to 10% in the intervention arm with 5% significance level and 80% and 90% power respectively. Calculations were also based on a 55% and 60% reduction in oropharyngeal gonorrhoea positivity. To detect a 50% reduction in oropharyngeal gonorrhoea positivity with 80% power, a total of 438 men will be required (i.e. 219 in each arm). This is a conservative effect size because our pilot data suggest that a single-dose of mouthwash is associated with a five-fold decrease in detection of gonorrhoea [86]. To allow for up to 15% loss of follow up [94], we will recruit a total of 504 men, 252 in each group. This will ensure 80% power to detect a 50% reduction in oropharyngeal gonorrhoea positivity from 20% to 10%, and 90% power to detect a 50% reduction from 25% to 12.5%.

**Table 1 Tab1:** Sample size calculations assuming 20% in the control arm will have a positive NAAT for oropharyngeal gonorrhoea within 12 weeks

Efficacy of mouthwash	Oropharyngeal gonorrhoea positivity in the intervention arm	Number of participants	
		80% Power	90% Power
50% reduction	10%	438	572
55% reduction	9%	356	464
60% reduction	8%	294	380

Calculations were based on 5% significance level

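### Recruiting 504 men preserves the required 438 only up to about 13% loss, not the stated 15%; the effect on power is under one percentage point

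*Protocol article*

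**What the plan says.** All the relevant statements are in the Sample size section of the protocol article and its Table 1.

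- Control-arm assumption: "we assumed oropharyngeal gonorrhoea positivity by NAAT in the arm using mouthwash B to be 20% over 12 weeks".
- Target: a fall "from 20% in the control arm to 10% in the intervention arm with 5% significance level and 80% and 90% power respectively".
- Evaluable number at 80% power: "a total of 438 men will be required (i.e. 219 in each arm".
- Allowance for loss: "To allow for up to 15% loss of follow up [94], we will recruit a total of 504 men, 252 in each group".
- Power claimed for the recruited number: "This will ensure 80% power to detect a 50% reduction in oropharyngeal gonorrhoea positivity from 20% to 10"%, and also "90% power to detect a 50% reduction from 25% to 12.5"%.

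Three other sections bear on how many men would be analysed. Loss to follow-up defines a lost participant as one who has not made the week 12 visit by week 14. Statistical methods puts every man with one or more follow-up swabs into the primary intention-to-treat analysis. Primary analysis compares the arms by logistic regression and mentions no continuity correction.

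**The concern.** The step from 438 to 504 adds 15% of the evaluable number. A loss rate applies to the men recruited, so the required number has to be divided by the fraction retained. The two operations differ, and the one used gives too few men for the loss rate named.

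The sentence also makes a promise: at a loss of up to 15%, the required number and both power figures are said to be secure. Anyone monitoring retention against that limit would take 14% or 15% loss to be covered in full. By the protocol's own requirement, the cover stops earlier.

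**Working it through.** **Inputs** (Sample size section unless noted): control 20%, intervention 10%, 5% significance, 80% power, 438 evaluable, 15% loss, 504 recruited; second scenario 25% against 12.5% at 90% power. Allocation is 1:1 (Sequence generation). Sidedness is not stated; two-sided is the choice that reproduces the table.

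**1. Reproduce the plan's 438.** Per arm, with d = p1 − p2 and p̄ the mean proportion:

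n′ = [1.960·√(2p̄(1−p̄)) + z·√(p1(1−p1) + p2(1−p2))]² / d²

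n = (n′/4)·[1 + √(1 + 4/(n′d))]² (continuity correction)

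For 20% against 10% at 80% power (z = 0.842): n′ = [1.960 × 0.505 + 0.842 × 0.5]² / 0.01 ≈ 199.0. The correction gives n ≈ 218.5, so 219 per arm and 438 in total, as stated.

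The same formula reproduces every cell of Table 1: 438/572, 356/464 and 294/380. Other versions of the 438 cell do not match: two-sided uncorrected gives 398, unpooled variance 394, and one-sided corrected 354. The two-sided continuity-corrected formula is therefore evidently the one used.

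For 25% against 12.5% at 90% power it also gives 219 per arm (218.5 before rounding), 438 in total. Both power claims therefore rest on 438 evaluable men, with nothing spare beyond rounding.

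**2. Reproduce the plan's 504.** 438 × 1.15 = 503.7, rounded up to 504.

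**3. Inflate for loss among those recruited.** 438/0.85 = 515.3, so 516 in two equal arms (258 each). That is 12 more than 504 (12/504 = 2.4%).

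**4. What 504 covers.** 1 − 438/504 = 66/504 = 13.1%. At 15% loss, 504 × 0.85 = 428.4, so about 428 men (214 per arm), 10 short of 438.

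**5. Power at 214 per arm.** Inverting the correction gives n′ = (n − 1/d)²/n. Power is Φ{[d√n′ − 1.960·√(2p̄(1−p̄))] / √(p1(1−p1) + p2(1−p2))}.

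- 20% against 10%: n′ = (214 − 10)²/214 = 194.5; power 79.1%.
- 25% against 12.5%: n′ = (214 − 8)²/214 = 198.3; power 89.3%.

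The uncorrected figures use n = 214 in place of n′. The last two rows enumerate all possible outcomes.

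| Method | Men per arm | 20% v 10% | 25% v 12.5% |
|---|---|---|---|
| Continuity-corrected formula | 219 | 80.1% | 90.1% |
| Continuity-corrected formula | 214 | 79.1% | 89.3% |
| Uncorrected formula | 214 | 82.8% | 91.5% |
| Exact, Pearson chi-square | 214 | 83.4% | 91.9% |
| Exact, Yates-corrected chi-square | 214 | 80.0% | 89.8% |

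**The case against.** The strongest reply is that nothing of practical weight follows, and most of it stands.

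- **Planned test.** The comparison is by logistic regression, which behaves more like the uncorrected test than the corrected one. On that basis 428 men give 82.8% and 91.5%, above both targets. The uncorrected formula needs only 398 men for the main scenario, so the cautious sizing method absorbs the slip.
- **Size.** Even by the sizing formula the shortfall is 0.9 points (80 − 79.1) and 0.7 points (90 − 89.3). Control positivity is itself uncertain enough that the protocol considers both 20% and 25%.
- **Analysis set.** Loss is defined by the week 12 visit, but a man with a week 6 swab stays in the primary analysis if he misses week 12. At 15% loss about 76 men are lost (504 − 428). If 10 of them (10/76, about 13%) had an earlier swab, 438 would be analysed. The documents do not give that proportion, so 428 is not a firm analysable number. In the other direction, such men have less time under test for an endpoint of detection at any time within 12 weeks, so they do not fully replace completers.

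A reader might infer from the arithmetic that the trial is underpowered, or that it misses its 80% and 90% targets outright. The documents do not support that. The shortfall appears only under the continuity-corrected calculation, and only if every lost man contributes nothing.

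What remains is independent of the test chosen: 504 × 0.85 is below 438. The article states a loss tolerance, and on its own requirement the tolerance is wrong. An analysis plan not shown here would not alter that sentence.

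**Conclusion.** The point holds as a minor arithmetic error. The number recruited preserves the stated 438 evaluable men up to about 13% loss, not 15%. At a full 15% loss with no data from those men, about 428 remain. Power by the plan's own formula is then under one point below each figure said to be ensured, and by a calculation closer to the planned analysis it is above both. There is no material loss of power.

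This rests on three assumptions: a two-sided 5% test (inferred from Table 1), loss spread equally over the arms, and lost men contributing nothing to the primary analysis. The third is pessimistic given the analysis set, so the number analysed may exceed 428.

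**What to change.** Keep 504 and change one sentence in the Sample size section, in either of two ways:

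- State that 504 men allow for up to about 13% loss to follow-up while retaining 438.
- Keep the 15% and state its consequence: about 428 men remain, giving 79% power (20% against 10%) and 89% power (25% against 12.5%) by the continuity-corrected formula, or 83% and 91% uncorrected.

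The cost is one sentence and a slightly less favourable figure. Recruitment, design and analysis do not change. Recruiting 516 would also restore the stated 15% allowance, at the price of 12 more men, but the power figures do not make that necessary.
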